### Study Design and Settings

We designed a nonrandomized pragmatic intervention study targeting people diagnosed with T2DM who were treated with MDI. This before-and-after intervention was designed to assess the real-world applicability of a precision medicine algorithm. Rather than using a control group, this study uses each participant as their own control, comparing clinical outcomes before and after the intervention. The intervention was adapted to be integrated into routine clinical workflows across both primary and specialized care settings.

This study is being conducted within 21 primary health care centers of the Catalan Health Institute (Institut Català de la Salut) in the Lleida health care region (Catalonia, Spain; Multimedia Appendix 1) together with the Department of Endocrinology and Nutrition, University Hospital Arnau de Vilanova, as the reference tertiary center.

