### Data Collection and Management

#### Overview

Data for this study are collected from electronic medical records and patient-reported questionnaires during study visits. Clinical and demographic information, including age, sex, educational level, BMI, diabetes duration, comorbidities, complications, and current pharmacological treatment, is obtained from the eCAP (electronic medical record) software and supplemented by medical interviews. Laboratory variables, including C-peptide, GADAb, HbA_1c_, and estimated glomerular filtration rate, are extracted from recent laboratory reports or requested when unavailable. CGM data, including metrics such as time in range, hypoglycemia episodes, and glucose variability, are downloaded directly from the devices used by participants throughout the study. Patient-reported outcomes, including quality of life, treatment satisfaction, medication adherence, and physical activity, are assessed using validated questionnaires. All study variables and corresponding time points are summarized in Table 1. In addition, detailed information on the study variables, including their definitions and data sources, is provided in Multimedia Appendix 2.

**Table 1. T1:** Study timeline, variables, and procedures.

Data collected	Evaluation time point			
	Preselection	Visit 0—inclusion	Visit 1—intervention (2 weeks)	Visit 2—final follow-up (6 months)
Inclusion and exclusion criteria	✓	✓		
Sociodemographic data^a^		✓		
Anthropometric data^b^		✓		✓
Clinical data^c^		✓		✓
CGM^d^ data			✓	✓
Laboratory data^e^		✓		✓
Smoking status		✓		
Pharmacological treatment^f^		✓		✓
Severe hypoglycemia^g^		✓		✓
Questionnaires^h^		✓		✓

a Age, gender, primary care center, current occupational status, level of education, number of children, date of menopause, and whether the participant is the sole caregiver of another person.

b Weight, height, BMI, and abdominal circumference.

c Arterial hypertension, dyslipidemia, micro- and macrovascular complications, heart failure, and renal disease of any etiology (estimated glomerular filtration rate <60 mL per minute per 1.73 m2).

d CGM: continuous glucose monitoring.

e Inclusion visit: hemoglobin A_1c_ (HbA_1c_), glutamic acid decarboxylase autoantibody, glycemia, and C-peptide; final visit: HbA_1c_.

f Prescription and dosage of diabetes drugs.

g Inclusion visit: last 12 months; final visit: 6 months of study.

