### Study Outcomes

We defined the primary study outcome as the proportion of participants in whom prandial insulin is successfully discontinued after the application of the therapeutic algorithm and who remain without prandial insulin at the final visit (6 months).

Secondary outcomes encompass several domains. Glycemic control following therapeutic optimization is evaluated through changes in HbA_1c_ and CGM-derived metrics, including time in range and time below range. Patient-reported outcomes are also assessed by comparing changes from baseline to 6 months after the intervention, including changes in quality of life (using the Diabetes Quality of Life Questionnaire), treatment satisfaction (using the Diabetes Treatment Satisfaction Questionnaire, both status and change versions), medication adherence (measured using the Adherence to Refills and Medications Scale), and physical activity levels (evaluated using the Spanish version of the International Physical Activity Questionnaire).

Safety outcomes include the number of severe hypoglycemic episodes at the final visit 6 months after the intervention compared with the 12-month period before enrollment. The study also examines the predictive value of CGM metrics by analyzing their association with pancreatic reserve and insulin resistance considering both continuous and categorical variables.

Finally, among patients who continue prandial insulin and CGM use for 6 months, the study assesses the impact of CGM on glycemic control (HbA_1c_ and CGM metrics), as well as changes in quality of life, treatment satisfaction, and medication adherence.

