### Sample Size and Statistical Analysis

At the time of the study planning, data from the Lleida health care region had identified 1388 people with T2DM treated with MDI. On the basis of prior clinical experience, approximately 25% of these individuals may have sufficient residual β cell function to discontinue prandial insulin. To estimate this proportion with a 95% CI and a margin of error of –5% to +5%, a sample size of 239 participants was estimated.

The study population will be characterized at baseline with respect to age, BMI, duration of diabetes, presence of chronic diabetes-related complications (microvascular and macrovascular), and cardiovascular risk factors. In addition, in-depth phenotyping will be performed using the homeostatic model assessment of β cell function and homeostatic model assessment of insulin resistance indexes [27] and GADAb measurements.

For the primary outcome, the proportion of participants who discontinue prandial insulin after the application of the diagnostic algorithm and sustain this change over a 6-month follow-up period will be calculated, along with its corresponding 95% CI.

Secondary outcomes will include measures of glycemic control, patient-reported outcomes, and safety outcomes. Glycemic control will be assessed using HbA_1c_ and CGM-derived metrics, including time in range (70‐180 mg/dL), time below range, time above range, mean glucose, and glycemic variability indexes. Patient-reported outcomes will include validated scores for treatment satisfaction, adherence, and quality of life analyzed according to each instrument’s scoring manual. Safety outcomes will include the incidence of severe hypoglycemia.

To evaluate changes over time (eg, from baseline to follow-up visits), paired 2-tailed *t* tests or Wilcoxon signed-rank tests will be used depending on data distribution. Between-group comparisons (eg, discontinuation vs continuation of prandial insulin) will be conducted using Student *t* tests or Mann-Whitney *U* tests as appropriate, as well as using linear mixed-effects models to account for within-subject correlation.

For categorical secondary outcomes, including severe hypoglycemia, comparisons between groups will be performed using chi-square or Fisher exact tests as appropriate. For outcomes measured repeatedly across follow-up visits, analyses will be conducted using linear mixed-effects models.

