CGM variables will also be examined as potential predictors of pancreatic reserve and insulin resistance. Depending on whether outcomes are continuous or categorical, linear or logistic regression models will be applied. Results will be expressed as regression coefficients or odds ratios with corresponding 95% CIs.

Loss to follow-up will be quantified and reported as the proportion of participants without outcome data at each follow-up time point. When available, reasons for loss to follow-up will be documented. Baseline characteristics of participants with complete follow-up and those lost to follow-up will be compared to assess potential differential attrition. A complete-case analysis will be used as the primary analytical approach when the proportion of missing data is low, and missingness will be considered compatible with a missing completely at random mechanism. To account for potentially informative missingness, multiple imputation by chained equations will be performed under a missing-at-random assumption, including all variables used in the main analyses and auxiliary variables related to missingness.

All statistical analyses will be performed using the R software (version 4.1.2; R Foundation for Statistical Computing), with a 2-sided *P* value of <.05 considered statistically significant.

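### Severe hypoglycemia, the only safety outcome named, is compared as a 6-month count against a 12-month count with no common time scale, so an unchanged rate looks like a halving

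*Protocol article*

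**What the plan says.** Four places in the protocol article bear on this outcome.

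- **Study Outcomes** defines it as a count, the number of "severe hypoglycemic episodes at the final visit 6 months after the intervention compared with the 12-month period before enrollment".
- **Table 1, footnote g** (Data Collection and Management, Overview) shows that the data are collected over those same windows: "Inclusion visit: last 12 months; final visit: 6 months of study".
- **Sample Size and Statistical Analysis** describes it differently: "Safety outcomes will include the incidence of severe hypoglycemia". No person-time denominator is given. The same section then treats the outcome as categorical: "For categorical secondary outcomes, including severe hypoglycemia, comparisons between groups will be performed using chi-square or Fisher exact tests as appropriate". For change over time in general it names paired t "tests or Wilcoxon signed-rank tests will be used depending on data distribution". The significance criterion is a two-sided P "value of <.05 considered statistically significant".
- **Study Design and Settings** makes the before-after contrast the core of the design: "Rather than using a control group, this study uses each participant as their own control, comparing clinical outcomes before and after the intervention".

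**The concern.** A number of episodes grows with the time over which it is collected. Here the period before is twice as long as the period after, and the outcome is worded as a number. Read literally, the comparison favors the intervention by construction: part or all of any observed fall is due to the shorter window. It also fails as a safety check, because an increase in the rate has to exceed a doubling before the raw count rises at all.

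This matters because the study's hypothesis and discussion turn on whether prandial insulin can be stopped safely, and the article expects the strategy to reduce hypoglycemia. Severe hypoglycemia is the one safety outcome named in support of those statements. There is no control group measured over the same two windows that would expose the artefact.

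**Working it through.** **The plan's own figure.** The article gives no rate or count for severe hypoglycemia, so there is none to reproduce for this outcome. The sample size used below does reproduce. For a 25% proportion with a 5-point margin, n0 = 1.96² × 0.25 × 0.75 / 0.05² = 288.1. With the finite population of 1388, 288.1 / (1 + 287.1/1388) = 238.7, rounded up to 239.

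**Inputs.** From the article: 12 months before, 6 months after, n = 239, two-sided 0.05 (2.5% in each direction). Assumed: event rates R of 0.05 to 0.5 per person-year, and either a common rate (Poisson) or strong clustering of episodes in few people (negative binomial, shape k = 0.2).

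**Step 1: counts.** Expected count = n × R × window length.

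- No change in rate: (R × 0.5) / (R × 1) = 0.50, whatever R is.
- Rate truly doubled: (2R × 0.5) / (R × 1) = 1.00.
- Example at R = 0.20: 239 × 0.20 × 1 = 47.8 episodes before and 239 × 0.20 × 0.5 = 23.9 after.

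**Step 2: any episode, yes or no.** The share with at least one episode over window w is 1 − exp(−Rw) under Poisson and 1 − (1 + Rw/k)^(−k) under the negative binomial. With no change in rate:

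| R per person-year | Poisson: 12 mo / 6 mo | Ratio | Clustered: 12 mo / 6 mo | Ratio |
|---|---|---|---|---|
| 0.05 | 4.88% / 2.47% | 0.51 | 4.36% / 2.33% | 0.53 |
| 0.10 | 9.52% / 4.88% | 0.51 | 7.79% / 4.36% | 0.56 |
| 0.20 | 18.13% / 9.52% | 0.53 | 12.94% / 7.79% | 0.60 |
| 0.50 | 39.35% / 22.12% | 0.56 | 22.16% / 14.97% | 0.68 |

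The apparent fall runs from 49% (ratio 0.506) to 32% (ratio 0.676).

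**Step 3: significance, if the general paired tests are applied to raw counts.** Simulation with n = 239, no true change and 3000 runs per setting. Entries are the percentage of trials showing a significant decrease (paired t / Wilcoxon).

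| R per person-year | 6 vs 12 months, Poisson | 6 vs 12 months, clustered | Equal windows, Poisson | Equal windows, clustered |
|---|---|---|---|---|
| 0.05 | 29.5 / 29.5 | 27.2 / 27.1 | 2.9 / 2.9 | 2.6 / 2.6 |
| 0.10 | 52.5 / 52.4 | 50.3 / 50.2 | 2.6 / 2.6 | 2.5 / 2.5 |
| 0.20 | 82.6 / 82.1 | 78.1 / 76.9 | 2.4 / 2.3 | 2.5 / 2.8 |
| 0.50 | 99.4 / 99.3 | 99.1 / 98.9 | 2.2 / 2.2 | 3.5 / 3.4 |

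With equal windows the error returns to about the nominal 2.5%, so the excess comes from window length alone.

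**The case against.** **The scaling may be settled elsewhere.** The analysis section speaks of *incidence*, which can mean a rate per unit of time. Variable definitions are deferred to Multimedia Appendix 2, and a statistical analysis plan may exist; neither is shown. This limits the claim to the visible text. It does not remove the point: the article itself fixes the comparison as a number over 6 months against 12, and elsewhere handles the outcome as categorical. That is a stated comparison that misleads, and not merely an omitted detail.

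**The error rates are not the plan's.** This stands. A reader might infer that the study carries a 27–99% false-positive risk on safety. The article assigns no before-after test to severe hypoglycemia; the paired t and Wilcoxon tests are named only for change over time in general, and the event rates are assumed. Step 3 is therefore conditional. Only the 0.50 ratio follows from the article alone.

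**The between-group test is sound in this respect.** A reader might extend the criticism to the chi-square or Fisher comparison. At follow-up both groups share the same nominal 6-month window, so unequal windows do not bias it. It answers a different question and cannot stand in for the before-after comparison.

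**It is a secondary outcome.** This is true. The primary outcome is a proportion with its confidence interval and is untouched. Both window lengths are disclosed, so a careful reader could annualize. Even so, a safety comparison should not depend on the reader making that correction.

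**Conclusion.** The point holds for the before-after comparison of severe hypoglycemia as the article words it. The no-change ratio of counts is 0.50, which needs only a constant rate and complete windows of 12 and 6 months. The exact halving applies to counts; for any episode yes or no the artefact is smaller and depends on the assumed rate and clustering (step 2). The effect on significance tests is conditional on both the assumed rates and the use of the general paired tests.

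Two stronger readings are not supported. The article does not say that this is the only safety outcome: both relevant sections say that safety outcomes *include* it, and time below range is listed separately under glycemic control. Nor does the article show that the authors will leave the counts unscaled, only that no visible text scales them. The wording should be corrected before the formal analysis begins.

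**What to change.** Define the before-after outcome as severe hypoglycemic episodes per person-year. Report a within-person rate ratio with 95% CI, for example from a Poisson or negative binomial GEE model with a log person-time offset, a period term and clustering on participant. The offset also handles participants followed for less than 6 months. Alternatively, where episode dates allow, count only the last 6 months before enrollment and compare equal windows.

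Align the two descriptions so that Study Outcomes and the analysis section name the same measure, with its denominator. The between-group chi-square or Fisher comparison at follow-up can stay.

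The cost is wording in the analysis plan. The counts and nominal windows are already collected, and the Results section says that formal analysis starts only after follow-up is complete. One weakness remains: recall over the 12 months before enrollment is likely to be less reliable than recording during follow-up. A rate scale does not cure this, so it should be stated as a limitation.

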A randomized controlled trial by Rosenstock et al [15] demonstrated that, in people with T2DM, discontinuing prandial insulin and initiating a once-weekly glucagonlike peptide-1 receptor agonist led to improved glycemic control approaching normoglycemia, reduced hypoglycemia, decreased body weight, and improved quality of life. Similarly, the BEYOND trial by Giugliano et al [16] evaluated switching from basal bolus insulin regimens to a glucagonlike peptide-1 receptor agonist or a sodium-glucose cotransporter type 2 inhibitor. Comparable glycemic control was achieved with lower total insulin doses, fewer daily injections, and reduced hypoglycemia, along with improved weight management and patient satisfaction. A comprehensive review by Giugliano et al [17] including these and other studies confirmed that insulin therapy can be simplified in persons with T2DM without compromising glycemic control while reducing treatment complexity, hypoglycemia risk, and polypharmacy.

Continuous glucose monitoring (CGM) has been evaluated in both randomized trials and real-world studies involving people with T2DM treated with multiple daily insulin injections (MDI), basal insulin, or noninsulin regimens [18,19]. In Catalonia (northeast Spain), the public implementation of CGM for people with T2DM on MDI was approved in November 2023. This required collaboration and coordination between different care providers, constituting an opportunity to develop and implement this protocol in routine clinical practice [20].

This project proposes implementing a precision medicine algorithm for persons with T2DM treated with MDI in real-world clinical practice. This algorithm incorporates assessment of pancreatic autoimmunity and residual β cell function (pancreatic reserve) into the decision-making workup.

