### Study Procedures and Timeline

Potential participants were identified by local study physicians and nurses using the primary care eCAP (Catalan Health Institute) electronic clinical record software. Each participant underwent 4 study visits. Initially, a preselection visit was conducted through electronic health record review without direct patient contact. Eligible individuals were then contacted and provided with detailed study information. Those who agreed to participate were invited to the inclusion visit (visit 0), during which written informed consent was obtained by research staff. This visit involved a clinical interview, a physical examination, laboratory testing (including C-peptide and GADAb measurements), and the placement of a CGM device. All participants used CGM for 10 to 15 days prior to the intervention. Two weeks later, the first follow-up visit (visit 1) was conducted. At this visit, therapeutic decisions were made based on C-peptide and GADAb results, and treatment was adjusted according to the predefined therapeutic intervention algorithm (Figure 1).

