#### Questionnaires

Several validated questionnaires are used to assess patient-reported outcomes related to quality of life, treatment satisfaction, medication adherence, and physical activity. These questionnaires are administered at both the baseline and final study visits (6 months), as outlined in the study timeline (Table 1).

A detailed description of each questionnaire, including constructs assessed, number of items, scoring, and references, is provided in Table 2.

**Table 2. T2:** Summary of patient-reported outcome questionnaires used in this study.

Questionnaire	Construct measured	Description and domains	Number of items	Response scale	Scoring and interpretation	Time points	Reference
ESDQoL^a^	Diabetes-related quality of life	Assesses multiple domains of diabetes-specific quality of life, with domain impact weighted by patient-reported importance	43	5-point Likert scale	Weighted average score; higher scores indicate poorer quality of life	Baseline and 6 months	[22]
DTSQs^b^	Diabetes treatment satisfaction	Measures satisfaction with current diabetes treatment; includes separate items on perceived frequency of hyperglycemia and hypoglycemia	8	7-point Likert scale (0 to 6)	Sum of 6 items (range 0 to 36); higher scores indicate greater satisfaction; 2 items analyzed separately	Baseline and 6 months	[23]
DTSQc^c^	Change in treatment satisfaction	Assesses perceived change in satisfaction compared with previous treatment	8	7-point Likert scale (–3 to +3)	Positive scores indicate improvement; negative scores indicate deterioration	6 months	[23]
ARMS-e^d^	Medication adherence	Evaluates adherence behaviors and barriers related to medication use	12	4-point Likert scale (“never” to “always”)	Lower total scores indicate better adherence	Baseline and 6 months	[24]
IPAQ^e^	Physical activity	Assesses physical activity in the previous 7 days, including walking, moderate and vigorous activity, and sedentary behavior	7	Frequency (d per wk) and duration (min per d)	Physical activity expressed as MET^f^ min per week; higher values indicate higher activity levels	Baseline and 6 months	[25]

a ESDQoL: Spanish Diabetes Quality of Life Questionnaire.

b DTSQs: Diabetes Treatment Satisfaction Questionnaire–Status Version.

c DTSQc: Diabetes Treatment Satisfaction Questionnaire–Change Version.

d ARMS-e: Adherence to Refills and Medications Scale–Spanish Version.

e IPAQ: International Physical Activity Questionnaire–Short Form (Spanish version).

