## Discussion

### Expected Findings

According to data from the Catalan Agency for Health Quality and Assessment and the eCAP electronic medical record system, the Lleida health care region has approximately 27,769 individuals diagnosed with T2DM, representing 8.95% of the adult population. Among these patients, 5% are currently treated with MDI.

This study aims to improve the available evidence in precision medicine for T2DM, specifically targeting patients treated with MDI. Using the simple precision medicine algorithm (Figure 1) proposed in this study based on assessment of β cell function (C-peptide) and autoimmunity (GADAb), we will evaluate whether prandial insulin can be safely removed or replaced by another treatment in real-world clinical practice.

The study’s main outcome is the proportion of patients in whom prandial insulin is successfully discontinued and remains unnecessary at 6 months. Secondary outcomes include clinical measures such as HbA_1c_ levels; CGM-derived metrics related to insulin resistance and pancreatic function; incidence of severe hypoglycemia; and several patient-reported outcomes—including quality of life, treatment satisfaction, medication adherence, and physical activity. Among patients who continue prandial insulin and CGM, the study also examines the added value of CGM use on both metabolic control and patient experience.

The algorithm is implemented by a multidisciplinary research team—including general practitioners, endocrinologists, and nurses—who integrate biomarker results with patient-specific clinical characteristics to guide medical decision-making. The strategy proposed by this study is intended for inclusion in clinical practice. If successful, this approach could be adopted by health care professionals managing T2DM to achieve simpler, safer, and more effective treatment strategies, particularly those that offer cardiovascular, renal, and weight management benefits.

This personalized strategy aligns with a broader innovation trend in diabetes care. Similar to the study by Dennis et al [28], which developed and validated a predictive model to individualize glucose-lowering therapies in T2DM, our project aims to move beyond conventional treatment algorithms by incorporating patient-specific pathophysiological characteristics.

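### The 'impact of CGM' outcome is an uncontrolled change in participants selected for continuing CGM for 6 months, and for CGM metrics its baseline is recorded during CGM wear

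*Protocol article*

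**What the plan says.** The last secondary outcome under Study Outcomes reads: "among patients who continue prandial insulin and CGM use for 6 months, the study assesses the impact of CGM on glycemic control". It covers HbA1c, CGM metrics, quality of life, treatment satisfaction and adherence. The Discussion (Expected Findings) restates it causally: "the study also examines the added value of CGM use on both metabolic control and patient experience".

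Under Study Procedures and Timeline, the inclusion visit (Visit 0) includes laboratory testing "and the placement of a CGM device", and then: "All participants used CGM for 10 to 15 days prior to the intervention". Table 1 marks CGM data at Visit 1 and Visit 2 only. These data "are downloaded directly from the devices used by participants throughout the study". HbA1c and the questionnaires are scheduled at Visit 0 and at 6 months.

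Study Design and Settings says that there is no control group and that each participant is their own control. The statistical section plans paired t tests or Wilcoxon signed-rank tests for change over time. Under Intervention Algorithm, participants who stop prandial insulin typically stop CGM as well.

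**The concern.** The words 'impact' and 'added value' promise an effect of CGM. Two stated features stand in the way.

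- **Selection after baseline.** The set is defined by continuing both prandial insulin and CGM for 6 months, not by the decision at Visit 1. Someone who gives up the sensor in month 2, or stops prandial insulin in month 4, drops out of the set by definition. If giving up is related to response, the mean change in those who remain is shifted, and nothing in the design corrects it.
- **Baseline during wear (CGM metrics only).** The 'before' value for time in range is recorded while the participant is already wearing a sensor. If participants could see their readings, any early benefit is already in the baseline.

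Without a comparator, regression to the mean, study participation and other care (for example, specialist referral of suspected type 1 cases) also enter the change. A significant paired test could therefore be reported as evidence for CGM when it is not.

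**Working it through.** **1. Baseline for each endpoint**

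| Endpoint | First value | Last value | Relation to study sensor |
|---|---|---|---|
| HbA1c | Visit 0 | Visit 2 | baseline at inclusion, when the sensor is placed |
| Status questionnaires | Visit 0 | Visit 2 | baseline at inclusion |
| CGM metrics | Visit 1, from 10 to 15 days of wear | Visit 2 | baseline during wear |

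The baseline problem is therefore confined to the third row. The selection problem and the missing comparator apply to all three.

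**2. Does the missing-data plan repair the selection?** No. It provides for attrition comparison, complete-case analysis and multiple imputation. Imputation fills in absent outcomes of people who belong to the set. It does not restore people whom the definition excludes, such as someone who stopped CGM but has a 6-month HbA1c.

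**3. Can other participants serve as a comparator?** No. Those who stop prandial insulin typically stop CGM too, so CGM use is tied to insulin regimen and biomarker group.

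**4. Illustration of the selection shift.** The article gives no sizing for this outcome. Its only sizing figure reproduces:

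- n0 = 1.96² × 0.25 × 0.75 / 0.05² = 288.1
- with the finite population correction, 288.1 / (1 + 287.1/1388) = 238.7, rounded up to the stated 239.

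If 25% stop prandial insulin, about 0.75 × 239 = 179 continue.

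Suppose the true effect is zero, a share π of the 179 persist, and a normal latent tendency to persist has correlation ρ with the change score. The mean change in persisters is then shifted by ρ × φ(z)/π SD, where φ is the standard normal density and z the cut-off that leaves a share π. The rejection rate treats the SD as unchanged by selection. Both π and ρ are assumptions.

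| π | φ(z)/π | Shift, ρ = 0.1 | Shift, ρ = 0.3 | Rejection rate at two-sided 5% |
|---|---|---|---|---|
| 0.9 | 0.195 | 0.019 | 0.058 | 5.7% to 11.5% |
| 0.8 | 0.350 | 0.035 | 0.105 | 7.0% to 24.1% |
| 0.7 | 0.497 | 0.050 | 0.149 | 8.6% to 38.5% |

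**5. Direction for CGM metrics.** Let δ be the true gain in SD units, f the share already present during the run-in, and s the selection shift. On a simple additive view the observed change is (1 − f)δ + s, which differs from δ by s − fδ. The two terms oppose each other when persisters are the better responders. With f = 0.5 (assumed) and s between 0.019 and 0.149, they cancel at δ = s/f, that is, between 0.04 and 0.30 SD. Below that point the gain is overstated, and above it understated. The documents give none of f, s and δ, so the sign is open.

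**The case against.** **The phrase may only name a treatment branch.** Under the algorithm, those not stopping prandial insulin continue MDI and CGM, and 'for 6 months' could simply be the follow-up length. The Discussion restatement omits it. This is a fair alternative reading, but the outcome definition as written makes 6-month continuation a condition of membership. If the branch was meant, saying so costs nothing.

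**The uncontrolled design is disclosed.** It is, and the Limitations section says that causal inference may be limited. That caveat is tied to convenience recruitment, selection bias, centre variability and algorithm flexibility. It does not mention the continuation condition, the baseline during wear or the missing comparator, and the causal wording remains.

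**The run-in may have been masked.** The article does not say, and a condensed article can leave this to the full protocol or its appendix. Masking would largely remove the baseline objection for CGM metrics. This part of the point is therefore conditional.

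**Stronger readings that the documents do not support**

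- A reader might infer that the whole outcome lacks a baseline before CGM. HbA1c and the questionnaires have a Visit 0 baseline.
- A reader might infer that many participants already used CGM, because "the public implementation of CGM for people with T2DM on MDI was approved in November 2023" and recruitment began in January 2024. Prior use is not an exclusion criterion, but nothing says that any participant had it, and the article presents the approval as the opportunity for this protocol. No dilution figure can be drawn from that.
- A reader might infer a shift of 0.19 to 0.35 SD from dropping 10% to 20% of participants. That requires exactly the worst responders to stop, which is perfect selection.

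**Conclusion.** The point holds in a limited form. As written, the outcome selects on behaviour after the Visit 1 decision in a design without a control group, so it estimates a within-person change in persisters and cannot carry the words 'impact' or 'added value'. For CGM metrics, and only if the run-in was not masked, the contrast is also change during CGM use rather than change from before it.

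Neither the size nor the net direction can be derived from the documents. A reader might conclude that the CGM-metric result is biased toward zero. That does not follow, because selection of persisters can push the other way. The range of 0.02 to 0.15 SD, with rejection rates of about 6% to 39% under a true effect of zero, is an illustration. It rests on assumed persistence of 70% to 90%, an assumed correlation of 0.1 to 0.3 and 179 continuers.

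This is a secondary outcome. The primary proportion, its confidence interval and the sample size are untouched. The change is worth making because it is cheap and removes an avoidable selection and an unsupported causal claim.

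**What to change.** - **Analysis set:** all participants kept on prandial insulin and CGM by the decision at Visit 1, regardless of later persistence. Report 6-month persisters as a sensitivity analysis.
- **Main glycaemic measure for this question:** the already scheduled HbA1c change from Visit 0 to 6 months.
- **CGM metrics:** keep them, labelled as change during CGM use, and state whether the run-in was masked.
- **Wording:** in Study Outcomes and Expected Findings, replace 'impact' and 'added value' with uncontrolled within-person change.
- **Optional:** if CGM start dates can be obtained, a sensitivity analysis excluding prior users. Start date is not among the Table 1 variables, so this may need a retrospective look-up.

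**Cost:** a change of definition and wording, with no new study visits. The article places formal analysis after the end of follow-up, so the set can be fixed beforehand if analysis has not yet begun. The estimate may be slightly less favourable. Participants who stop CGM will lack 6-month CGM metrics and contribute only HbA1c and questionnaires. The number without CGM metrics should be reported.
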